## Abstract

**Background:**

Multimodal physical exercises already have well-established benefits for the post-stroke population that influence gait functional capacity, balance, gait, cognition, and quality of life. This type of intervention can be performed in both real and virtual environments. Considering the characteristics of both environments, it is questioned to what extent the combination of interventions in real and virtual environments could result in improvement in post-stroke impairments.

**Methods/design:**

We will conduct a randomized clinical trial with three groups: a real multimodal group (RMG), a virtual multimodal group (VMG), and a combined multimodal group (CMG). It was estimated that we will need a sample of 36 participants (12 per group). RMG individuals will only perform multimodal physical exercises in a real environment two times per week for 60 min per session for 15 weeks. VMG individuals will perform exercises of the same duration over the same time frame but only in a virtual environment. CMG individuals will hold a weekly session in a real environment and another weekly session in virtual environment. The primary outcome measure will be health-related quality of life, evaluated using the Stroke Impact Scale; effects on cognition (Montreal Cognitive Assessment), balance (Berg Balance Scale), mobility (Timed Up & Go), self-selected gait speed (10-meter walk test), and gait functional capacity (6-min walk test) will be investigated as secondary outcome measures. Participants will be evaluated before the beginning of the intervention, immediately after the end of the intervention, and at 1-month follow-up without exercise. If the data meet the assumptions of the parametric analysis, the results will be evaluated by analysis of variance (3 × 3) for the group factor, with repeated measures while taking into account the time factor. The post hoc Tukey test will be used to detect differences (α = 0.05).

**Discussion:**

This study represents the first clinical trial to include three groups considering physical exercise in real and virtual environments, isolated and combined, that counterbalances the intensity and volume of training in all groups. This study also includes a control of progression in all groups along the 15-week intervention. The outcome measures are innovative because, according to International Classification of Functioning, Disability and Health, activity and participation are the targets for effectiveness evaluation.

**Trial registration:**

Combinação de exercícios físicos multimodais em ambientes real e virtual para indivíduos pós acidente vascular cerebral crônico, RBR-4pt72m. Registered on 29 August 2016.

**Electronic supplementary material:**

The online version of this article (10.1186/s13063-019-3396-2) contains supplementary material, which is available to authorized users.

## Background

The diverse impairments observed after a stroke, associated with the reduction of intrinsic motivation and the presence of preexisting or acquired comorbidities, lead to a vicious cycle of decreased activity and increased exercise intolerance. As a consequence, secondary complications, such as reduced cardiorespiratory fitness, muscle atrophy, osteoporosis, and circulation impairment in the lower extremities, may occur and generate greater dependence in the activities of daily living and impact the social interactions of these individuals [1].

Different modalities of physical exercises already have well-established benefits for individuals after chronic stroke, including repercussions for cardiovascular capacity [2], muscle strength [3, 4], balance [5, 6], gait [7, 8], and cognition [9]. In order to maximize the effects of the exercises, there is a tendency to investigate the effects of multimodal protocols. According to Saunders et al. [10], a multimodal protocol refers to interventions based on the combination of physical exercises of different components, such as cardiorespiratory, muscular strength, and flexibility.

Multimodal physical exercises can be performed in both real and virtual reality environments. The interventions performed in real environments are the most commonly used in the clinical context. Characteristics of interventions performed in real environments include a high interactive relationship between the professional and the patient, high ecological validity, the possibility of individual or group applications, not requiring technological resources, and the ability to be applied in the home according to each patient’s needs.

Conversely, virtual reality-based interventions present features such as an environment rich in visual and auditory information with immediate and multisensory feedback [11], real-time simulation of tasks or environments, three-dimensional interactive and immersive experiences, a computerized interface, active and safe patient participation [12], and the ability to provide information with an external focus of attention [13, 14]. In a systematic review, Laver et al. [15] found that the addition of virtual reality to conventional methods resulted in improved upper limb function. However, they also found insufficient evidence regarding the superiority of virtual reality for promoting walking speed and balance. They were unable to pool results related to cognition, improvement of social participation, and health-related quality of life (HRQoL) because few studies included assessments of cognition and HRQoL to achieve meta-analysis requirements for these outcomes [15]. Therefore, these parameters should be investigated in future studies; in addition, the authors also emphasized the need for training lasting longer than 15 h of intervention and that future studies should set the number of participants screened for eligibility criteria.

Considering the characteristics of both environments, it is questioned to what extent the combination of interventions in the real and virtual environments could result in improvement in post-stroke impairments. There are few studies that have sought to find answers to this question. In the Shin et al. [16] study, the control group performed 1 h of occupational therapy per session, and the experimental group performed 30 min of occupational therapy plus 30 min of virtual reality. The results showed positive effects in both groups, except for the domain related to the limitations due to physical problems measured by the Short Form Health Survey scores, in which experimental group (EG) obtained greater benefits. Rajaratnam et al. [17] found positive results for balance and mobility measurements for the group that performed 40 min of conventional therapy plus 20 min of self-directed virtual reality balance training per session, compared with the control group, which performed 60 min of conventional therapy.

Saposnik and Levin [18] claimed there were few publications regarding the combination of multimodal physical exercises in real and virtual environments. Most of the existing studies did not investigate long-term effects, including follow-up, and added intervention time to the experimental groups, which provided them with an advantage in the total intervention time received. In addition, there is an important diversity in the literature regarding the profile characteristics of individuals with stroke, considering acute, subacute, and chronic patients. Thus, the results found in the previous studies [19–24] do not allow consistent conclusions to be made about the effects of the combination of multimodal exercises in real and virtual environments in individuals after chronic stroke.

This study seeks to answer whether the combination of multimodal physical exercises in real and virtual environments could bring additional benefits to the quality of life, cognition, gait, and balance of individuals after chronic stroke. We also intend to clarify the effects of interventions with multimodal physical exercises when performed only in a real environment or only in a virtual environment and to investigate whether the possible effects remain after 1 month without participating in physical exercises.

This study aims to investigate the effects of a protocol of multimodal physical exercises in real and virtual environments for individuals who have survived a stroke.

## Methods/design

### Trial design

This is a prospective, randomized, single-blind trial of a 15-week exercise program to investigate the effects of the combination of physical exercise in real and virtual environments for chronic post-stroke individuals. It was approved by the Ethics and Research Committee on Human Beings of the School of Physical Education and Sports at the University of São Paulo (CAE no. 40,688,114.9.0000.5391) and is registered with ensaiosclinicos.gov (no. RBR-4pt72m).

All participants and/or their relatives will provide written informed consent prior to participant enrollment. A Consolidated Standards of Reporting Trials (CONSORT) flow diagram of the trial is shown in Fig. 1, and a Standard Protocol Items: Recommendations for Interventional Trials (SPIRIT) checklist is provided in Additional file 1.

**Fig. 1 Fig1:**
[figure not shown]
Consolidated Standards of Reporting Trials (CONSORT) flow diagram

### Study setting

A prospective, randomized trial with concealed allocation, blinded assessors, and intention-to-treat analysis will be carried out. The study will be conducted in the Motor Behavior Laboratory in the School of Physical Education and Sports at the University of Sao Paulo, Brazil.

### Eligibility screening

Participants will be recruited from the waiting list for the rehabilitation program at the Physical Education and Sports School in Sao Paulo, Brazil, and will be screened for eligibility by neurological rehabilitation physiotherapy specialists.

### Inclusion and exclusion criteria

Screening will be done to obtain personal data for the individuals (name, sex, date of birth, address, telephone, and schooling), medical history, brain injury topography, and type of locomotion. After this initial screening, the individuals will be referred for a specific medical evaluation in order to investigate their health conditions, request the necessary tests, and follow the medicines used. Only those individuals who receive medical release for the practice of physical exercises will enter the study.

The inclusion criteria will be chronic phase stroke (more than 6 months post-stroke, according to Bernhardt et al. [25]), territory of the lesion in the middle cerebral artery or anterior cerebral artery, both types of stroke (ischemic and hemorrhagic), cognition greater than 24 points on the Mini Mental State Examination, at least 2 months of noninvolvement in other structured forms of physical exercise intervention (community), and no experience in virtual reality games.

The exclusion criteria will be individuals with any type of cardiovascular complication that would contraindicate physical exercise, individuals who underwent surgeries to attenuate clinical conditions resulting from stroke, and those who have undergone chemical blockade to reduce spasticity.

### Informed consent

Individuals who fit the study requirements will receive the informed consent form, which will be duly read and explained by the researcher and signed by the individuals and/or their legal guardians.

### Randomization procedures

Participants who meet the study inclusion criteria will be randomized into one of three sample groups—the real multimodal group (RMG), the virtual multimodal group (VMG), or the combined multimodal group (CMG)—through a draw of numbered (generated by computer) and sealed opaque envelopes. The evaluators have no knowledge of the results of the individual allocation (blinded evaluators). However, the same is impossible to perform with the professionals who will perform the interventions; because the interventions are supervised and progressive, there are clearly distinct protocols between groups of individuals.

To characterize the individuals, the Mini Mental State Examination, Fugl-Meyer Assessment, and Orpington Prognostic Scale will be applied. The individuals will also be characterized by the demographic variables of sex, age, type of stroke, injury time, affected brain hemisphere, and schooling.

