### Measurements

*Quality of life* will be evaluated through the SIS. This scale evaluates quality of life by measuring 59 items categorized in 8 domains: strength (4 items), hand function (5 items), activities of daily living/instrumental activity of daily living (10 items), mobility (9 items), communication items [7], emotion (9 items), memory and reasoning (7 items), and participation function (8 items). Each item is rated on a 5-point Likert scale in terms of difficulty the patient has experienced in completing each item. Summative scores will be generated for each domain, ranging from 0 to 100. An extra question will be asked in order to know, on a scale from 0 to 100, how much the individual feels they have recovered since their stroke. Our primary outcome measure will be the domain of the activities of daily living/instrumental activity of daily living, and the rest of the domains will be used as secondary outcome measures [34]. The Brazilian version of SIS 3.0 has satisfactory internal consistency, test-retest reliability, convergent validity, and discriminant validity in stroke patients [34]. SIS 3.0 is a specific measure of psychometrically robust HRQoL that can be useful in assessing the consequences of stroke in different cultural contexts [34]. For some of the domains that make up this scale, there are values of minimum detectable change (MDC) and clinically important difference (CID). According to Lin et al. [35], the values are strength (MDC 24.0 and CID 9.2), activities of daily living/instrumental activities of daily living (MDC 17.3 and CID 5.9), mobility (MDC 15.1 and CID 4.5), and hand function (MDC 25.9 and CID17.8).

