### Statistical analysis

It was estimated that a sample of 36 participants (12 per group) would provide 88% power (α = 5%) to detect a difference between group means of 17.3 (MDC of the activities of daily living/instrumental activities of daily living domain of the SIS) using the program G*Power 3 [48], which takes into account the number of sample groups and the number of evaluation measures. To reach this total number of individuals, at least 43 individuals must be recruited, allowing a dropout rate of 20%.

For the mathematical treatment and statistical analysis of the data, Excel software (Microsoft, Redmond, WA, USA) will be used for the tabulation of data, and SPSS version 13 software (SPSS, Chicago, IL, USA) will be used for statistical analyses. A significance level of 5% will be adopted. Initially, for the characterization of the sample, descriptive analysis and the *t* test will be used to examine differences between the RMG, VMG, and CMG groups. Subsequently, for the analysis of the normality and homogeneity of the results of the primary outcome measure and secondary outcomes, the Shapiro-Wilk and Levene tests will be used, respectively. After observing the assumptions for normality and homogeneity, parametric analysis will be performed using two-way analysis of variance (3 groups by 3 moments [baseline, post-test, and follow-up]) and post hoc Tukey test. The mean between-group difference and 95% confidence intervals will be reported for all outcomes. If any subject gives up the protocol, their measured outcomes will be analyzed on an intention-to-treat basis.

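### Allocation is an envelope draw with no stratification described; with 12 per arm, chance gaps in the starting ADL score will often exceed the plan's own clinically important difference

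*Protocol article*

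**What the plan says.** Under Randomization procedures, participants are assigned to the real, virtual or combined group "through a draw of numbered (generated by computer) and sealed opaque envelopes". Study setting adds that allocation is concealed and assessors are blinded. No block size, stratum or minimisation factor is described anywhere in the article. The severity scales have a descriptive role only: "To characterize the individuals, the Mini Mental State Examination, Fugl-Meyer Assessment, and Orpington Prognostic Scale will be applied".

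The abstract and Statistical analysis plan 36 participants, 12 per group, sized "to detect a difference between group means of 17.3" points with 88% power at a 5% level. Measurements gives the thresholds for the primary domain: "activities of daily living/instrumental activities of daily living (MDC 17.3 and CID 5.9". In Table 1 the SIS is marked in the Baseline column, which stands before the Allocation column.

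The analysis is a two-way ANOVA, three groups by three moments with baseline as one of the moments, followed by Tukey comparisons. No baseline covariate is named.

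**The concern.** The baseline value of the primary outcome is available when the envelope is opened, yet no use of it in allocation is described. The population is mixed: both stroke types, any time beyond six months, and no motor or ADL severity criterion (cognition and medical fitness for exercise are restricted). With 12 per arm, a plain draw leaves the starting ADL level of each arm to chance.

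A chance gap then reaches the results. A group main effect or a Tukey comparison of groups averages over the baseline moment and carries the gap with it. The group-by-time term allows for it only in part. Readers of a small three-arm trial will also look first at the baseline table, and a visible gap on the primary score weakens whatever is concluded.

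A second and smaller question is whether anything in the described procedure secures the planned 12 per group.

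**Working it through.** **1. The plan's own figure.** The 88% cannot be run forward, because no SD, effect size f or within-person correlation is given; the article says only that the program's calculation is one "which takes into account the number of sample groups and the number of evaluation measures". Solving backwards with 36 participants, a difference of 17.3 and alpha 0.05:

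- One-way F test on (2, 33) df reaches 88% at f = 0.602. With the third mean midway, f = 17.3/(SD × √6), so SD = 11.7. With one arm apart from two equal arms, f = 17.3 × √2/(3 × SD), so SD = 13.6.
- Repeated-measures between-group test, three measures, correlation 0.5 assumed: f = 0.491, so SD = 14.4 to 16.6.
- Group-by-time interaction, same assumption: f = 0.269, so SD = 26.3 to 30.3.

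I use 11.7 to 20. The upper end is an assumption. An interaction-based SD would make baseline gaps more frequent.

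**2. Chance gap at baseline.** With equal arms of 12, the difference between two arm means has SD = SD × √(2/12) = 0.41 SD. With balanced allocation within two median strata and a normal score, a share 2/π = 0.64 of the variance is balanced, leaving SD × √(2/12 × (1 − 2/π)) = 0.25 SD. Simulated chance of a gap of at least 5.9 points:

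| SD | Named pair, plain draw | Some two of three, plain draw | Some two of three, two median strata |
|---|---|---|---|
| 10 | 15% | 32% | 5% |
| 11.7 | 22% | 43% | 11% |
| 13.5 | 28% | 53% | 19% |
| 16.6 | 38% | 66% | 33% |
| 20 | 47% | 75% | 46% |

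At SD 8 the plain-draw figure would be only 17%. If all 43 recruits are counted (about 14 per arm), the chance is a little lower: 39% at SD 12 and 72% at SD 20, against 45% and 75% with 12 per arm.

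**3. What a gap does to each comparison.** Let r be the correlation of baseline with each later score, assumed 0.5 to 0.7. A starting gap of 5.9 leaves, in expectation:

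- post-test comparison: r × 5.9 = 3.0 to 4.1 points;
- group mean over three moments: (1 + 2r)/3 × 5.9 = 3.9 to 4.7 points;
- change from baseline: (r − 1) × 5.9 = −3.0 to −1.8 points, an over-correction.

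**4. Precision.** Variance of an arm difference, relative to an unadjusted post-test comparison:

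- Post-test with stratum: 1 − r² × 2/π = 0.84 (r = 0.5) or 0.69 (r = 0.7). The SE is 1 − √0.84 = 8% to 1 − √0.69 = 17% smaller.
- Change from baseline: 2(1 − r) = 1.00 or 0.60. With stratum: 2(1 − r) − (1 − r)² × 2/π = 0.84 or 0.54. The SE is 1 − √(0.84/1.00) = 8% to 1 − √(0.54/0.60) = 5% smaller.
- Baseline score as covariate: 1 − r² = 0.75 or 0.51, lower than any of the above.

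**5. Arm sizes.** If every participant is drawn independently, P(12/12/12) = 36!/(12!³ × 3³⁶) = 0.0226, and the smallest arm has 9 or fewer in 54% of trials. Average power then falls from 88% to about 86%. Restriction hardly alters the baseline gap: at SD 13 it is 51% with fixed 12/12/12 and 52% with an independent draw.

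**The case against.** The strongest objection is that the lack of restriction is read from silence. The article does not call the draw unrestricted, and a fixed pool of 12 envelopes per arm fits its words and its planned group sizes. A condensed article may also leave sequence details to a fuller protocol. This stands. A reader might infer that the trial uses simple randomisation with unequal arms; the document does not support that, so the arm-size point is conditional. The stated method is nevertheless a draw, and a fixed pool would still leave the starting score to chance.

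A reader might also infer that chance gaps rival the effect the trial is sized for. They do not: a gap of 17.3 points or more between some two arms occurs in about 0.5% of trials at SD 13.5 and 9% at SD 20. The frequent gaps are those at the 5.9-point level. Nor is this bias: allocation is random and concealed, so over repetitions the comparison is centred correctly.

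It is also fair that baseline is already a time level, so the group-by-time term absorbs much of a gap. At r = 0.7 a change contrast (0.60) even beats a stratified post-test comparison (0.69). What remains is the 5% to 8% gain over a change contrast, and the fact that group main-effect and Tukey comparisons carry the gap.

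Finally, Trial status puts the start of recruitment at August 2016 and its end in the first half of 2019, so few allocations may be left to change.

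**Conclusion.** The point holds as a design improvement. The article describes an envelope draw and no stratification, for 12 per arm, with the primary score already in hand. At SDs of 11.7 to 20, some two of the three arms would start at least one clinically important difference apart in about 43% to 75% of trials, against about 11% to 46% with two strata split near the median. Stratification therefore reduces the problem without removing it.

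The loss is one of precision and credibility. With a baseline-outcome correlation of 0.5 to 0.7, using the stratum makes the SE about 8% to 17% smaller than in an unadjusted post-test comparison, and about 5% to 8% smaller than in a change contrast. These figures rest on an SD and a correlation that the article does not give, a roughly normal score, and a cut near the median. The arm-size issue is separate, depends on how the envelopes were filled, and costs little power.

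**What to change.** **Allocation, for participants not yet allocated.** Use a computer-generated list of permuted blocks, sizes 3 and 6 mixed, within two strata of the pre-allocation SIS ADL/IADL score, with the cut fixed in advance. Number the envelopes consecutively within each stratum and open them in order, after the baseline visit is complete. If blocks or strata are already in use, one sentence under Randomization procedures settles the matter.

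**Analysis, for all participants.** Include the stratum, or better the baseline ADL score itself, in the between-group comparison at post-test and follow-up. This also works for people already allocated and recovers most of the lost precision.

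**Cost.** A new list and two sets of envelopes, with no added participant, visit or measurement. Predictability rises slightly, which mixed block sizes limit, and unfinished blocks can leave arms one or two participants apart. The gain shrinks if the cut misses the median: a 70/30 or 80/20 split captures 58% or 49% of the baseline variance instead of 64%, and the article gives no score distribution from which to set the cut. If recruitment is nearly complete, the allocation change will have little effect.
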